### Statistical analysis

Missing data and skewed data will be handled similar as in the economic evaluation study, hence respondents for whom at least 75% of the data per measurement instrument are available will be included in the analysis and missing data on item level will be handled using SPSS missing value analysis. Completely missing measurements will be handled using multiple imputation (MI). Arithmetic means will be used to describe cost data, and presented. In case of skewed cost data, non-parametric bootstrapping will be used to test for statistical differences in costs between the intervention and control group. The bootstrap replications will be used to calculate 95% confidence intervals around the costs (95% CI), based on the 2.5 and 97.5 percentiles. If cost data are distributed normally, t-tests will be used.

Concerning the cost measurements, a month of missing data exists between T2 and T3 and 6 months of missing data exists between T4 and T5. To deal with the issue we will use interpolation to construct new data points for these periods. This will be done by calculating mean cost data for the period of 6 months (T3) to 12 months (T4) post stroke and the period of 18 months to 24 (T5) months post stroke. These data will be used to estimate the period between 12 months to 18 months post stroke.

We will do a comparative analysis to estimate differences in costs between 1 year post stroke and 2 years post stroke. Additionally, we will compare cost outcomes and effect outcomes on the primary outcome scales. Furthermore, we will try to determine *high-cost users *and *low-cost users *of health care after stroke. In the latter analysis, *high-cost users *and *low-cost users *will be identified by specific patients' characteristics, costs being the dependent variable and patient characteristics being independent variables.

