#### Record linkage study (RLS)

A RLS will be conducted in which the stroke cases registered in the Maastricht University Medical Centre (MUMC) Stroke Register, MUMC Medical Administration, the Mental Health Case Register (MHCR) and GP registrations in the same catchment area, will be linked. Since the available data linking these registers is limited, linking these databases will provide updated and extended information about the current estimates of care consumption and the hypothesis that problems occurring after stroke, such as depression, anxiety and dementia are underestimated and under-diagnosed. The aim of this study is to examine how patterns of health care consumption after stroke (in terms of health care costs, productivity costs, costs of informal care) change during the 5 years after stroke, in comparison with the 5 years before stroke and what the economic impact is of these changes from a societal perspective.

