### Sample size calculation

Sample size calculation was not performed because all available patients will be used for data analysis.

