### Cost analysis and valuation

Through anonymous record linkage health care consumption within the 10-year reference period (from 5 years before and after stroke) will be analysed. The first step in the analysis is to examine this consumption before, during and after stroke. In an additional analysis the health care costs will be calculated based on quantities derived from the MHCR and GP registrations. The updated Dutch manual for cost analysis in health care research [39] will be used for the valuation of these health care costs.

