### Statistical analysis

The statistical processing program SPSS will be used to link all databases. Databases will be linked anonymously, meaning that specific codes based on different variables will be computed and used to compare patients, instead of specific patient information. To estimate health care consumption before and after stroke, we will divide all stroke patients in 2 equal groups. Therefore, high-cost users of health care after stroke will be compared to low-cost users of health care after stroke. Similar as in the COI-study, we will estimate the differences between high-cost users and low-cost users using regression analysis.

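### The record linkage study ties its before-after estimate to halves formed on cost after stroke; any change reported by half would be distorted by regression to the mean

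*Protocol article*

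**What the plan says.** The aim of the record linkage study (protocol article, Record linkage study) is to examine how patterns of health care consumption "change during the 5 years after stroke, in comparison with the 5 years before stroke".

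Two later sections bear on how this is done:

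- Cost analysis and valuation: "The first step in the analysis is to examine this consumption before, during and after stroke". No grouping and no estimator are named.
- Statistical analysis: "To estimate health care consumption before and after stroke, we will divide all stroke patients in 2 equal groups". The groups are defined in the next sentence: "high-cost users of health care after stroke will be compared to low-cost users of health care after stroke". The section then says that, as in the cost-of-illness (COI) study, "we will estimate the differences between high-cost users and low-cost users using regression analysis".

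The COI study's own Statistical analysis section describes its user analysis with "costs being the dependent variable and patient characteristics being independent variables".

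No sample size or cost distribution is given for the linkage study: "Sample size calculation was not performed because all available patients will be used for data analysis".

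**The concern.** The stated purpose of the split is to estimate consumption before and after stroke, and the split is made on consumption after stroke. Patients enter the high half partly because their post-stroke cost happened to be high relative to their own usual level, and the low half for the opposite reason. Their pre-stroke costs were not selected in this way and lie closer to the overall mean. A before-after change computed inside either half therefore mixes any effect of stroke with the effect of selection. The difference between the halves in post-stroke consumption exists by construction.

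The before-after result is the aim of this sub-study, and the Discussion lists it as a strength that will be compared with a 2001 linkage study. Changes shown by half could be read as two care trajectories following stroke when part or all of the pattern comes from how the halves were formed.

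**Working it through.** **Inputs.** From the document: two equal groups; groups defined by cost after stroke; target is the 5 years after compared with the 5 years before. The plan states no figure to reproduce. Assumed, because the document does not give them: the before-after correlation r, the skewness of costs (lognormal, CV 1 or 2) and otherwise equal distributions before and after. I read two equal groups of high-cost and low-cost users after stroke as a split at the median of post-stroke cost.

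**Normal costs, no true change.** The expected change is +(1 - r) × √(2/π) SD in the high half and the mirror image in the low half. With √(2/π) = 0.798:

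- r = 0.3: 0.7 × 0.798 = ±0.56 SD
- r = 0.5: 0.5 × 0.798 = ±0.40 SD
- r = 0.7: 0.3 × 0.798 = ±0.24 SD
- r = 0.9: 0.1 × 0.798 = ±0.08 SD
- r = 1: 0

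**Lognormal costs, no true change.** Let s be the log-scale SD, s = √ln(1 + CV²), r the log-scale correlation and Φ the normal distribution function. Relative to the overall mean, the high half has post-stroke mean 2Φ(s) and pre-stroke mean 2Φ(rs). The low half has 2[1 - Φ(s)] and 2[1 - Φ(rs)]. The after/before ratios are therefore:

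- high half: Φ(s) / Φ(rs)
- low half: [1 - Φ(s)] / [1 - Φ(rs)]

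Worked case, CV 1 and r = 0.5: s = √ln 2 = 0.833, Φ(0.833) = 0.7975, Φ(0.416) = 0.6614.

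- High half: 0.7975 / 0.6614 = 1.206
- Low half: 0.2025 / 0.3386 = 0.598

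This is about +20% and -40%. A simulation of 1,000,000 patients gave +20.3% and -40.2%. Simulated results for the other cases:

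| r (log scale) | CV 1: high / low half | CV 2: high / low half |
|---|---|---|
| 0.3 | +33% / -50% | +38% / -71% |
| 0.5 | +20% / -40% | +22% / -61% |
| 0.7 | +11% / -28% | +11% / -45% |
| 0.9 | +3% / -11% | +3% / -19% |

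In every row the change in all patients pooled was within 0.5% of zero.

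**A true rise of 50% in everyone (CV 1, r = 0.5).** Multiply the ratios by 1.5:

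- High half: 1.5 × 1.206 = 1.81, or +81%
- Low half: 1.5 × 0.598 = 0.90, or -10%
- Pooled: +50%

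At r = 0.7 the low half shows a rise of about 9% (1.5 × 0.723 = 1.085) and the high half +66%. The low half therefore need not fall, but its rise is understated and that of the high half overstated.

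**Splitting on pre-stroke cost instead** only reverses the sign: at CV 1 and r = 0.5 with no true change, the high half shows -17% and the low half +67%.

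**The case against.** The strongest case on the other side has four parts.

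1. *The biased contrast is not spelled out.* The only comparison the section names is high-cost against low-cost users after stroke, by regression. It does not name a pre-to-post change within each half or a test of change between halves. This stands, and it is why the point is conditional. It does not remove the point, because the opening clause gives before-after estimation as the purpose of the split, and nothing excludes such statements by half.

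2. *An ungrouped look is already planned.* The first step under Cost analysis and valuation names no groups, and a pooled comparison there would be free of the artefact. This also stands. But that step gives no estimator, and the section that does describe the method links before-after estimation to the split.

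3. *The regression may already be sound.* The linkage study refers to the COI study, where cost is the dependent variable. A reader might infer that the linkage regression uses the two-group variable as its outcome and so loses power. In one simulated example with an assumed predictor effect and 1,000 patients, power fell from 81% to 61%. The document does not establish that reading. The figure applies only if the two-group variable is the outcome.

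4. *All magnitudes rest on assumed values.* This is correct. The direction under no true change does not depend on them, provided r is below 1 and the cost distribution is otherwise the same before and after.

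Profiling who becomes a high-cost user is a legitimate descriptive aim and is not affected.

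**Conclusion.** The point holds in conditional form. As written, the linkage study's Statistical analysis section attaches the before-after estimate to halves formed on the after-period of that same contrast. Change reported within or between those halves would be biased: overstated in the high half and understated in the low half. With no true change the artefact is about +20% and -40% at CV 1 and r = 0.5. Over the assumed range (CV 1 to 2, r 0.3 to 0.9) it runs from +3% to +38% in the high half and from -11% to -71% in the low half.

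Two stronger readings are not supported. A reader might infer that the low half must always show a fall, but this is certain only when stroke changes nothing. A reader might also infer that the contrast is unrelated to any real effect of stroke. At CV 1 and r = 0.5, a true 50% rise moves the high half from about +20% to +81% and the low half from -40% to -10%, so a real effect does show, in distorted form. Nor does the document show that the whole before-after analysis is compromised, since the ungrouped first step may include a pooled estimate.

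The matter concerns an observational sub-study and affects neither randomised trial. It is worth correcting because the before-after change is that sub-study's aim.

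**What to change.** Reword the record linkage study's Statistical analysis section as follows:

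- Estimate the before-after change within patients, in all stroke patients together, and link this explicitly to the first step under Cost analysis and valuation.
- Make no before-after contrast, and no contrast in post-stroke consumption, between halves formed on post-stroke cost. Forming the halves on pre-stroke cost is no remedy.
- Use the high/low split only to profile users on pre-stroke and stroke characteristics.
- State that the regression follows the COI study, with continuous cost as the dependent variable and patient characteristics as independent variables.

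The cost is a small rewording and a presentation slightly less simple than a two-group table. No new data are needed.

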### Statistical analysis

The power analyses in both trial-based economic evaluations will be based on the RCTs. The primary (base-case) analyses will be performed according to the intention-to-treat principle. This means that data from all participants will be used, regardless of whether they received the intervention or not. For the analyses we will use SPSS statistical software and Excel.

Respondents for whom at least 75% of the data per measurement instrument are available will be included in the analysis. Missing data on item level will be handled using SPSS missing value analysis. Completely missing measurements will be handled using multiple imputation (MI). A baseline analysis will be performed to examine the comparability of groups at baseline for both costs and outcomes. If necessary, methods will be applied to control for differences in baseline [33]. Despite the usual skewed distribution of costs, the arithmetic means is generally considered the most appropriate measure for describing cost data [33]. Therefore arithmetic means (and standard deviations) will be presented. In case of skewed cost data, non-parametric bootstrapping will be used to test for statistical differences in costs between the intervention and control group. Non-parametric bootstrapping is a method based on random sampling with replacement based on the participants' individual data [34]. The bootstrap replications will be used to calculate 95% confidence intervals around the costs (95% CI), based on the 2.5 and 97.5 percentiles. If cost data are distributed normally, t-tests will be used.

ICERs will be calculated for both the CEA and CUA. The ICER will be calculated as follows: ICER = (Ci - Cc)/(Ei - Ec), where Ci is the annual total cost of the new intervention, Cc is the annual total cost of the comparator, Ei is the effects at the 6 month follow-up for the new intervention and Ec is the effect at 6 month follow-up for the comparator.

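### The record linkage study labels two equal halves of its patients high-cost and low-cost users, and leaves unsettled whether its regression models those halves or cost itself, as the cost-of-illness study does

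*Protocol article*

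**What the plan says.** Four statements in the protocol article bear on this.

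- Record linkage study, Statistical analysis: to estimate consumption before and after stroke, "we will divide all stroke patients in 2 equal groups". It continues: "Therefore, high-cost users of health care after stroke will be compared to low-cost users of health care after stroke". The word median does not appear and no cut-off is given.
- Same section, on the model: "Similar as in the COI-study, we will estimate the differences between high-cost users and low-cost users using regression analysis".
- Cost-of-illness study, Statistical analysis: high-cost and low-cost users are also to be identified, but by a regression with "costs being the dependent variable and patient characteristics being independent variables". No equal split is described.
- Trial-based economic evaluations, Statistical analysis: "Despite the usual skewed distribution of costs, the arithmetic means is generally considered the most appropriate measure for describing cost data".

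The record linkage study has no planned size: "Sample size calculation was not performed because all available patients will be used for data analysis".

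**The concern.** Two equal groups ranked by cost can only meet at the median. Such a split treats a patient just above the median like the most expensive patient in the register, and treats near-identical patients on either side of it as opposites. With right-skewed costs the median lies below the mean, so calling the upper half high-cost promises more than the grouping delivers.

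The regression is called similar to one that models cost itself. If the high/low indicator is the outcome, the two are not similar: one estimates how patient characteristics shift cost, the other how they shift the chance of being above the median. At stake is whether the analysis shows which patients drive cost after stroke, and whether it can be compared with the cost-of-illness results.

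**Working it through.** The article gives no patient number, cost mean, SD or power for this study, so there is no stated figure to reproduce. The distributions, CVs, log-SDs and simulated sample size below are assumptions.

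**1. Which variable is modelled?** There are two readings.
- The high/low indicator is the outcome. Then the analysis differs from the cost-of-illness regression it claims to resemble.
- Cost is the outcome. Then the split plays no part in the regression, and a difference between high-cost and low-cost users is not what the model estimates.

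The two statistical sections need reconciling under either reading.

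**2. How much of the upper half lies below the mean?**

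Lognormal cost with log-SD s has median exp(μ) and mean exp(μ + s²/2). The share of the upper half below the mean is therefore 2Φ(s/2) − 1. The top 10% of patients carry a share Φ(s − 1.2816) of all cost. CV² = exp(s²) − 1.

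| s | CV | Upper half below mean | Cost share of top 10% |
|---|---|---|---|
| 1.0 | 1.3 | 38% | 39% |
| 1.5 | 2.9 | 55% | 59% |
| 2.0 | 7.3 | 68% | 76% |

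With milder lognormal skew the share below the mean is 19% at CV 0.5, 32% at CV 1 and 47% at CV 2.

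Gamma cost with shape k = 1/CV² and unit scale has mean k, and the share is 2[F(k) − 0.5]: 13% at CV 0.5, 26% at CV 1 and 37% at CV 1.41.

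The overall range is about 13% to 68%. The size depends on the assumed skew. The direction does not, as long as the median lies below the mean.

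**3. Is information lost if the indicator is modelled?** This depends on the comparator. Take a weak predictor that shifts log cost.

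- *Against regression on normally distributed log cost.* Relative efficiency of the split is 2/π = 0.637, so the loss is 1 − 0.637 = 36%, and π/2 = 1.57 times as many patients are needed.
- *Against a mean-based model (raw means, or a gamma model with log link) with lognormal cost.* The split's efficacy is 2/(π s²) and the mean's is 1/CV², so the ratio is (2/π) × CV²/s².
  - s = 1.0: 0.637 × 1.718/1.00 = 1.09
  - s = 1.5: 0.637 × 8.488/2.25 = 2.40
  - s = 2.0: 0.637 × 53.60/4.00 = 8.53

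  The split is the more efficient analysis at all three. At CV 0.5 and CV 1 the ratio is 0.71 and 0.92, a loss of 29% and 8%.
- *Against a mean-based model with gamma cost.* With m the median, the ratio is 4(m f(m))²/k: 0.59 at CV 0.5 and 0.37 at CV 1.41, a loss of 41% to 63%.

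A simulation (assumed n = 400, binary predictor, lognormal cost, 2,000 runs) agrees:

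| Log-SD, log shift | Split | Log cost | Raw means |
|---|---|---|---|
| 0.83, 0.24 | 64% | 82% | 68% |
| 1.27, 0.37 | 65% | 83% | 51% |

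The entries are power.

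**The case against.** The strongest reply is that the text does not say the halves are regressed. It points to the cost-of-illness analysis, which also speaks of high-cost and low-cost users and keeps cost as the dependent variable, so the natural reading may be that cost stays continuous. This stands: the article contains an ambiguity, not an established wrong analysis.

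A reader might also infer that the split throws away about a third of the information. The document does not support that as a general statement. The 36% holds only if the indicator is modelled, and only against regression on normally distributed log cost. Against a mean-based model the loss can be larger, smaller or reversed, as shown above.

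It can further be said that labels relative to the median are a convention, that a top 10% or 20% is also arbitrary, and that the below-mean shares rest on assumed distributions. All true. But the article itself treats the mean as the appropriate summary of skewed cost, and gives no reason for calling half of all patients high-cost.

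Finally, the stakes are limited. The study is observational, costing is an additional analysis in which "the health care costs will be calculated based on quantities derived from the MHCR and GP registrations", and no treatment comparison depends on the split. A condensed article may leave model details to a fuller plan. The equal split and the claimed similarity, however, are stated in the article and do not fit together.

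**Conclusion.** The point holds in a limited form. It rests on the label, on what the regression estimates, and on consistency with the cost-of-illness analysis, not on precision.

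- The equal halves are above-median and below-median groups. That the cut falls at the median is an inference, though the only one that fits equal groups ordered by cost.
- Given the skew that the article expects, part of the upper half lies below the mean: about 13% to 68% under the assumed lognormal and gamma distributions. These are illustrations, not estimates for the registers.
- If the indicator is modelled, cost differences within each half are lost, the effect of patient characteristics on cost is not estimated, and the result cannot be set beside the cost-of-illness regression. If cost is modelled, these consequences fall away and only the wording and the label need repair.

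The change is worth making, but its reach is modest.

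**What to change.** In the Statistical analysis section of the record linkage study, state that cost is the continuous dependent variable, as in the cost-of-illness study, and prespecify a model suited to skewed costs. A generalised linear model with log link, or a two-part model if many costs are zero, would target mean cost. Log-cost regression can serve as a sensitivity analysis.

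Use any high/low grouping for description only, with one prespecified definition shared by the record linkage and cost-of-illness studies. A top share such as 10% or 20% is one option. Whatever is chosen should be justified.

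This changes the analysis wording only; the same linked data and software serve. The price is a slightly less simple presentation than two groups, and a mean-based model may give wider intervals when costs are very skewed. The reason to accept that is that it answers the question about cost.

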## Discussion

The Restore4Stroke programme aims not only to provide effective interventions, but will also help to identify stroke patients and their informal caregivers at risk of developing long-term problems and refer them to the proper health care professional. The major strength of this programme is that it allows us to combine several powerful research methods into a comprehensive study and to oversee our research outcomes from an aggregate level.

The Restore4Stroke programme is innovative for several reasons. First, the family-centred perspective results in investigating the quality of life in both patients and their informal caregivers. Second, the focus of Restore4Stroke on personal factors as possible determinants of long-term re-integration and on quality of life in a prospective longitudinal design is innovative in comparison with studies focussing on physical and functional consequences [40]. Third, the comprehensive and multidisciplinary character of Restore4Stroke should provide new and necessary information which can serve several different medical sciences and decision makers.

Within Restore4Stroke, the present study, €-Restore4Stroke, will provide new economic insights and evidence for the rehabilitation of psychosocial consequences occurring in the chronic phase after stroke. One of the strengths of the €-Restore4Stroke study is that we include the estimation of health effects on informal caregivers. By adding the CarerQOL questionnaire to our research we not only perform an actual full economic evaluation from a societal perspective, but we are also able to expose the true scope of effects shown by the Self-Management study. Another strength of this study is the inclusion of the RLS, which will give new insights in health care consumption five years before and five years after stroke. To our current knowledge, no RLS has been done recently, although more information has become available about the consequences of stroke. In addition, we will be able to compare our results to a RLS conducted in 2001 [41] and determine what has changed since. Furthermore, we expect that the information we gain from the economic evaluation of the two suggested interventions will add impact on the implementation of these interventions in health care.

